### Statistical analysis

All statistical analyses will be performed using STATA/IC 13.1 for Windows (StataCorp, College Station, TX, USA). Primary analysis will be based on intention-to-treat analysis. The primary endpoint will be tested using 90% confidence intervals with the PASDAS at week 16 as outcome, treatment group as determinant, and baseline values of PASDAS as covariate (ANCOVA). Missing values will be imputed where appropriate. Differences between groups on secondary outcomes will be tested with chi-square test (or Fisher exact test) for categorical variables (e.g., response criteria sets such as MDA and ACR 20/50/70) and with unpaired *t* test or non-parametric alternative (where appropriate) for continuous variables (e.g., DAPSA score, Quality of Life). Descriptive statistics will be provided using mean +/− SD, median (p25-p75) or percentages for primary and secondary outcomes, where appropriate.

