#### Secondary objectives

Key secondary objectives that will be investigated (between treatment groups at week 16):
The change in the different health domains of PsA (peripheral joint disease, enthesitis, dactylitis, axial involvement, and skin and nail psoriasis)The change in the Disease Activity in Psoriatic Arthritis (DAPSA) scoreThe difference in proportion of patients meeting minimal disease activity (MDA) criteria, low disease activity (LDA) according to PASDAS (≤ 3.2) and DAPSA (≤ 14), and American College of Rheumatology (ACR) 20/50/70 response criteriaThe difference in quality of lifeThe difference in adverse events (AEs)

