### Study design

The COMPLETE-PsA trial is designed as a randomized placebo-controlled double-blind superiority trial. Seventy-eight DMARD-untreated patients with PsA will be randomized 1:1 to either the combination arm (MTX and LEF) or the monotherapy arm (MTX and placebo). To ensure equal allocation of patients with high disease activity (HDA), patients will be stratified in both groups by PASDAS ≥ 5.4 (= cutoff score for HDA) at baseline. This because regression to the mean is more likely to occur in patients with HDA and, from a biological point of view, treatment might be more effective in patients with HDA.

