### Randomization, concealment, and blinding

Patients will be allocated to either MTX plus LEF (intervention) or MTX plus placebo (control) at baseline visit, stratified by PASDAS ≥ 5.4 (HDA). Patients will be allocated using stratified variable block randomization, to prevent predictability of allocation. Randomization is performed by a research physician or research nurse using a computerized randomization procedure. Allocation is kept in sealed and consecutively numbered envelopes. Patients, physicians, researchers, and nurses will be blinded for treatment allocation. The distribution and assignment of study medication, based on randomization number, is done by the hospital pharmacy. The placebo is manufactured compliant with Good Manufacturing Practice (GMP) guidelines and the placebo tablets are indistinguishable from LEF tablets. If needed, unblinding is possible after consulting the hospital pharmacist. All quantities that participants have taken (evaluated by pill count) are documented. Before the disposal of used, unused, and depleted pill boxed, a pill count will be performed.

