### Sample size

The primary outcome for the study is the difference between the combination therapy group (MTX and LEF) and the monotherapy group (MTX and placebo) on the PASDAS at week 16. The sample size per arm for a *t* test having a power 1-β(=0.8) when testing at significance level α(=0.05) (one-sided) to detect a difference of δ is *N* = 2*(z_1-α_ + _z1-β_)^2^*SD^2^/δ^2^. Based on predefined response criteria for the PASDAS, the study was powered to detect a difference of δ = 0.8 [22]. The standard deviation of the PASDAS in PsA patients is reported to range from 1.31 to 1.63, we used the latter value in these calculation to be conservative [19]. One-sided testing was chosen because it is highly unlikely that a combination of MTX and LEF would be inferior (with regard to effectiveness) to MTX monotherapy. In addition, as it is not common practice to start with the combination therapy, the main focus of interest is to see if the combination is superior to methotrexate monotherapy (the first-line therapy to date). Furthermore, one-sided testing instead of two-sided testing leads to a reduction in patient numbers and costs. With these parameters, the required number of patients would be 52 per arm for a total of 104 patients. When correcting for baseline PASDAS score, this sample size can be reduced by (1-r^2^) where r is the correlation between baseline and follow-up. In addition, baseline PASDAS is a stratification factor, and therefore, should be adjusted for in the analysis. Based on information from the literature, the correlation between two PASDAS measurements is approximately 0.8 [22]. However, this correlation might be too optimistic, considering it is based on patients without changes in disease activity or treatment. Therefore, to protect for a too-optimistic correlation, a total trial size corresponding to a correlation of 0.5 was chosen. With this correlation of 0.5, a total number of 78 patients is required. The short follow-up of this trial will allow inclusion of additional patients should some drop out. No more than 10% (8 patients) dropout is expected, because of the short duration of the study, so the maximum number of patients to be included is 86 (43 patients per arm).

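### Binary secondary outcomes are tested without the PASDAS ≥ 5.4 randomisation stratum, which costs some power for the absolute-state outcomes; a stratified test recovers it at no cost.

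*Protocol article*

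**What the plan says.** Under Randomization, concealment, and blinding, the protocol states: "Patients will be allocated using stratified variable block randomization". The single stratification factor is high disease activity, defined as baseline PASDAS of at least 5.4. Study design gives as one reason that "regression to the mean is more likely to occur in patients with HDA", and adds that treatment may work better in that group.

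The Sample size section, while explaining how adjustment reduces the required number, remarks: "In addition, baseline PASDAS is a stratification factor, and therefore, should be adjusted for in the analysis".

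Statistical analysis puts this into practice for the primary endpoint, through an ANCOVA with baseline PASDAS as covariate. For the categorical secondary outcomes it says: "Differences between groups on secondary outcomes will be tested with chi-square test (or Fisher exact test) for categorical variables". Its examples are "response criteria sets such as MDA and ACR 20/50/70". Low disease activity by PASDAS (≤ 3.2) and by DAPSA (≤ 14), listed under Secondary objectives, is also binary and falls under the same sentence. The article gives no stratified or covariate-adjusted analysis for any binary outcome.

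**The concern.** If arms are balanced within strata and the stratum predicts the outcome, the treatment difference varies less from trial to trial than a pooled chi-square test assumes. That test counts the spread between strata as noise, although stratified randomisation has already removed it from the comparison. The test then rejects a true null less often than its nominal level and misses real effects more often.

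The link between stratum and outcome should be strongest for absolute states. A patient who starts with PASDAS above 5.4 has further to fall to reach 3.2 than one who starts at 4. DAPSA ≤ 14 and MDA are also fixed thresholds at week 16. ACR responses are improvements relative to the patient's own baseline, so the stratum may carry little information about them.

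What is at stake is power for responder outcomes that the protocol lists among its key secondary objectives, in a trial of 78 patients.

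**Working it through.** **The plan's own figure.** Sample size uses N per arm = 2(z₁₋α + z₁₋β)²·SD²/δ² with one-sided α = 0.05, power 0.80, SD 1.63 and δ = 0.8:

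2 × (1.645 + 0.842)² × 1.63² / 0.8² = 51.33, rounded up to 52 per arm (104 in total).

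Multiplying by 1 − r² with r = 0.5: 51.33 × 0.75 = 38.5, rounded up to 39 per arm, or 78. The figure reproduces. It concerns the primary endpoint only; no power is stated for any binary outcome.

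**Why the pooled test is conservative.** Let the strata have shares w and null response rates p, with overall rate p̄. The pooled test uses variance p̄(1 − p̄). With arms balanced within strata, the variance that applies is Σ w·p(1 − p). If k is the ratio of the second to the first, the actual two-sided error of a nominal 5% test is about 2[1 − Φ(1.96/√k)].

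The documents give no PASDAS means for this population. As an illustration, assume a baseline mean of 5.4 (half the patients in each stratum), a week-16 mean of 4.0, SD 1.63 and bivariate normality, with PASDAS ≤ 3.2 as the response.

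- r = 0.5: response is 16.6% in the high stratum and 45.8% in the low one, so p̄ = 0.312. Pooled variance is 0.312 × 0.688 = 0.2147. Within-stratum variance is (0.166 × 0.834 + 0.458 × 0.542)/2 = 0.1933. So k = 0.90, 1.96/√k = 2.065, and actual error is about 3.9% (simulated: 4.0%).
- r = 0.8: response is 6.3% and 56.0%, so p̄ = 0.3115. Pooled variance is 0.2145 and within-stratum variance is (0.063 × 0.937 + 0.560 × 0.440)/2 = 0.1527. So k = 0.71, 1.96/√k = 2.323, and actual error is about 2.0% (simulated: 2.2%).

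**Power.** Inputs from the protocol: 78 patients, 1:1 allocation within the PASDAS ≥ 5.4 strata, SD 1.63, effect 0.8, and r = 0.5 (planning) or about 0.8 (literature). Assumed: baseline mean 5.0, control improvement 1.0, the intermediate r = 0.7, and a two-sided 5% level, because the article sets no level for secondary outcomes. The implied response rates are Φ((3.2 − 4.0)/1.63) = 31% on control and Φ((3.2 − 3.2)/1.63) = 50% on combination. Simulation with uncorrected tests gives:

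| r | Chi-square, null | CMH, null | Chi-square, power | CMH, power |
|---|---|---|---|---|
| 0.5 | 4.3% | 5.1% | 39% | 43% |
| 0.7 | 3.1% | 4.8% | 39% | 48% |
| 0.8 | 2.7% | 5.0% | 38% | 52% |

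**Sensitivity.** Baseline means of 4.8 or 5.4, week-16 means of 3.2 to 4.5, SDs of 1.31 or 1.63 and a within-stratum odds ratio of 3 (all means and the odds ratio assumed) give:

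- r = 0.5: chi-square error 4.0–4.7%; CMH gains about 2 to 4 power points.
- r = 0.8: chi-square error 1.6–4.3%; CMH gains about 6 to 16 points.
- CMH error stays at about 4.8–5.1% throughout.

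**If the stratum is not prognostic.** With 25% response in both strata and an odds ratio of 3, power is about 64% for chi-square and 63% for CMH. Their error rates are about 5.1–5.3% and 4.9–5.1%. Stratifying then costs almost nothing.

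**The case against.** The strongest reply is that an unadjusted test of a secondary binary outcome is conventional and valid, and that at the planning correlation the gain is only about 4 power points on a test whose power stays near 40%. Both statements are true and limit the importance of the point. The larger gains need r = 0.7 to 0.8. The protocol itself calls the literature value of about 0.8 possibly too optimistic, because it comes from patients whose disease and treatment were stable.

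Four stronger readings are tempting but not supported:

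- *The protocol breaks its own rule.* A reader might take "baseline PASDAS is a stratification factor, and therefore, should be adjusted for in the analysis" as binding on every outcome. The sentence stands within the argument for reducing the primary sample size, and the ANCOVA carries it out. Its reasoning extends naturally to the secondary outcomes, but the protocol does not say that it does.
- *The results would be invalid.* The error rate moves below nominal, not above it.
- *All responder outcomes lose power.* Only PASDAS ≤ 3.2, the outcome tied most directly to the stratifier, was simulated. DAPSA ≤ 14 and MDA are expected to behave similarly, by a smaller or larger amount. ACR 20/50/70 should show little or no difference.
- *High disease activity would remain unbalanced.* Blocking within strata already deals with most of that.

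It is also fair to say that the unpaired t tests for continuous secondary outcomes share the omission. That is a related matter and does not weaken this one.

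**Conclusion.** The point holds as a matter of efficiency, of low to moderate importance. For PASDAS ≤ 3.2, the pooled chi-square test would reject a true null in about 4.3% of trials at r = 0.5 and about 3% at r = 0.7 to 0.8. It would give up about 4 power points at r = 0.5 (39% against 43%) and roughly 9 to 14 at the higher correlations (39% against 48%; 38% against 52%). The Fisher alternative would be more conservative still.

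These sizes rest on the assumed PASDAS means, control improvement and two-sided 5% level, and on approximate normality. The direction needs only that the stratum predicts the outcome. No claim of lost power is made for ACR 20/50/70.

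**What to change.** In Statistical analysis, replace the chi-square/Fisher test for binary secondary outcomes by a CMH test stratified by baseline PASDAS ≥ 5.4, reporting the Mantel-Haenszel risk difference with its confidence interval. Apply it to MDA, to PASDAS and DAPSA low disease activity and, for consistency, to ACR 20/50/70. State that no continuity correction is used, since the figures above assume none. Logistic regression with continuous baseline PASDAS may be added as a supportive analysis.

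The cost is one sentence. The stratum is already recorded for every patient at randomisation, and neither the sample size nor the data collection changes.

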During the development of this research protocol, there were different issues that needed to be addressed and choices that had to be made. To start, a primary outcome measure for this trial had to be chosen. So far, it is not clear what the most optimal outcome measure for clinical trials in PsA is. The optimal outcome measure would preferably be a continuous measure, that is disease-specific and includes the different domains of the disease. Furthermore, it has to be reliable and sensitive to change. For this trial, different outcome measures were considered, including: the DAPSA, the MDA criteria, the Composite Psoriatic Disease Activity Index (CPDAI), the ACR 20/50/70 response criteria and the PASDAS. Although the DAPSA is easy to calculate, it has unfavorable clinimetric properties. It is not parametrically distributed, has a large measurement error, does only take the peripheral joint disease domain into account, and it was unable to discriminate between treatment groups in two different studies, in contrast to ACR responses and MDA measurement [28, 29]. The MDA criteria result in a dichotomized outcome (fulfillment of the criteria, yes or no) and consequently the need of a larger sample size than would be needed with a continuous outcome measure. The CPDAI is a continuous outcome measure, but has less discriminative capacity than other outcome measures [30]. The ACR response criteria are not disease-specific, are dichotomous, and do not include all the PsA disease domains. Contrarily, the PASDAS is a disease-specific, continuous, reliable and valid outcome measure that includes most of the disease domains of PsA. The use of the PASDAS as a primary outcome measure is further enabled by the integration of routine and standardized PASDAS measurements in routine clinical practice [31]. Based on these considerations, the PASDAS was chosen as the primary outcome measure for this trial.

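### Continuous secondary outcomes are tested without covariate adjustment, although ANCOVA on each outcome's own baseline would be more precise at almost no cost

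*Protocol article*

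**What the plan says.** In the protocol article, the Statistical analysis section sets two standards for continuous outcomes. The primary outcome, PASDAS at week 16, is analysed by ANCOVA with baseline PASDAS as covariate. The continuous secondary outcomes are compared by an unpaired t "test or non-parametric alternative (where appropriate) for continuous variables (e.g., DAPSA score, Quality of Life"). No covariate is named for them.

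The Secondary objectives section words most of these outcomes as change: "The change in the different health domains of PsA", and likewise for DAPSA. The Abstract (Methods) does the same for DAPSA, skin, enthesitis, dactylitis and joint counts, and the section on skin and nail scores does so for the skin scores. Quality of life is worded as a difference between groups. Study visits at baseline, week 8 and week 16 (Assessments) supply the baseline values.

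The Sample size section relies on baseline adjustment for the primary outcome. It reduces the required number by the factor 1 − r², takes r = 0.5, and adds: "In addition, baseline PASDAS is a stratification factor, and therefore, should be adjusted for in the analysis".

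**The concern.** The plan recognises that a baseline covariate reduces the variance of the treatment comparison, and it uses this to reduce the trial from 104 to 78 patients. It does not use the same device for the continuous secondary outcomes, although their baseline values are available or are already needed to form the change scores.

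At stake is the width of the confidence intervals for the key secondary outcomes in a trial of about 39 patients per arm. A t test on change subtracts the whole baseline value, whatever its correlation with follow-up. A t test on week-16 values subtracts none of it. ANCOVA estimates how much to subtract. With equal variances, a chance baseline difference D shifts the week-16 comparison by rD and the change comparison by −(1 − r)D, which is +0.5D and −0.5D at r = 0.5. ANCOVA removes the linear part of that shift.

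**Working it through.** **Inputs** (protocol article, Sample size section)

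- Test and power: "power 1-β(=0.8) when testing at significance level α(=0.05) (one-sided").
- Effect: "the study was powered to detect a difference of δ = 0.8".
- SD: "The standard deviation of the PASDAS in PsA patients is reported to range from 1.31 to 1.63, we used the latter value".
- Reduction factor for baseline adjustment: 1 − r², with planning value r = 0.5 for PASDAS.
- 78 patients randomised 1:1 (Study design), so 39 per arm.

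**Step 1. Reproduce the plan's own figures.** Per arm, N = 2 × (1.645 + 0.842)² × 1.63² / 0.8² = 51.33, rounded up to 52, or 104 in total. This agrees with the plan: "the required number of patients would be 52 per arm for a total of 104 patients". With baseline adjustment, 104 × (1 − 0.5²) = 78, which also agrees.

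**Step 2. Relative variance of the treatment comparison.** Assume the same SD at baseline and week 16. In units of the variance of the week-16 comparison:

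- t test on week-16 values: 1
- t test on change: 2(1 − r)
- ANCOVA: 1 − r²

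At r = 0.5 these are 1, 1 and 0.75. Either t test therefore has 1 / 0.75 = 1.33 times the ANCOVA variance, a 25% loss of information. A t test on 78 patients is as precise as ANCOVA on 78 × 0.75 = 58.5.

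**Step 3. Vary r.** The documents give no correlation for DAPSA, joint counts, enthesitis, dactylitis, skin, HAQ, PsAID or SF-12, so r is an assumption for all of them. The loss is r² for week-16 values and 1 − (1 − r²) / [2(1 − r)] = (1 − r)/2 for change. The power columns are illustrative: standardised difference 0.8 / 1.63 = 0.49 (the PASDAS planning value), 39 per arm, one-sided 5%, normal approximation, power = Φ(0.49 / √(2v/39) − 1.645), with v the relative variance from step 2.

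| r | Loss, change | Loss, week 16 | Power, change | Power, week 16 | Power, ANCOVA |
|---|---|---|---|---|---|
| 0.3 | 35% | 9% | 57.4% | 69.9% | 73.5% |
| 0.5 | 25% | 25% | 69.9% | 69.9% | 80.4% |
| 0.7 | 15% | 49% | 87.6% | 69.9% | 91.8% |
| 0.8 | 10% | 64% | 96.3% | 69.9% | 97.5% |

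The article does not state the sidedness of the secondary tests. Two-sided at 5% and r = 0.5, the power is 58.2% for either t test and 70.6% for ANCOVA.

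**Step 4. Check by simulation.** In 10,000 simulated trials of 78 patients, stratified on the dichotomised baseline of the outcome itself, with r = 0.5 and a one-sided 5% test, power was about 71% for either t test and 80% for ANCOVA. Under no effect, the rejection rate was about 3.6% for the t tests and 4.9% for ANCOVA. The t tests are conservative here because they ignore the stratification. This is the extreme case, since the secondary outcomes are only partly related to PASDAS.

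**The case against.** The strongest reply is that the tests are valid under randomisation, that the trial was sized for PASDAS alone, and that no power is promised for any secondary outcome. All of this stands. The point is about efficiency.

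Four stronger readings are tempting, and the documents do not support them.

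- *The secondary tests ignore baseline.* Most of these outcomes are defined as change, and a test on change uses the baseline value, though not optimally. Stratified randomisation on PASDAS ≥ 5.4 also gives some balance on outcomes that are components of PASDAS.
- *The plan breaks its own adjustment rule.* The sentence on adjusting for the stratification factor stands in the Sample size section, which concerns the primary outcome, and the primary analysis follows it. Its reasoning would extend to other outcomes, but the plan does not say that it must.
- *A quarter of the information is lost, as a fact.* That figure needs r = 0.5, which is a cautious planning value for PASDAS only. It is also a normal-theory figure, so it is only approximate where a rank test is used.
- *Leaving the choice between t test and rank test open is a defect.* The Discussion says of DAPSA "It is not parametrically distributed, has a large measurement error", which fits with allowing a non-parametric alternative. The rule for choosing is detail that an article commonly leaves to the statistical analysis plan, which is not shown.

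What remains is that the article names a specific unadjusted method where a more precise one is available from data already collected.

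**Conclusion.** The point holds as an improvement that is nearly free; it is not an error that threatens the trial. The unadjusted comparison of continuous secondary outcomes is valid but less precise than ANCOVA. On the assumption that r = 0.5 applies to these outcomes, the variance is 1.33 times as large and 25% of the information is lost. Over r = 0.3 to 0.8 the loss is 35% to 10% for change scores and 9% to 64% for week-16 values. These figures assume equal variances at the two visits and a linear relation. ANCOVA has the smallest variance at every r in that range, apart from the degrees of freedom that it uses. A reader might infer bias in the secondary results, but the loss is in precision and power only. The primary analysis and N = 78 are unaffected.

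**What to change.** In the Statistical analysis section, replace the unpaired t test for continuous secondary outcomes by ANCOVA, with the week-16 value as outcome, treatment as factor, and as covariates the outcome's own baseline value and the stratification factor (baseline PASDAS or the PASDAS ≥ 5.4 stratum). For skewed scores, use a rank-based or transformed version of the same model; which one can be set out in the statistical analysis plan.

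The cost is one or two sentences, slightly more analysis work, and one degree of freedom per covariate. With two covariates the residual degrees of freedom fall from 78 − 2 = 76 to 78 − 4 = 74. No extra patients, visits or measurements are needed, and the sample size and primary analysis stay as they are.

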### Data collection and monitoring

The collected data will be entered in CASTOR, an electronic database set up for clinical trials (https://www.castoredc.com/nl/waarom-Castor.html). Data will be coded and kept based on the rules for good clinical practice (GCP) by certified personnel. Handling of personal data will comply with the Dutch Personal Data Protection Act (WBP, wetbescherming persoonsgegevens). Data of all centers will be monitored following the guidelines of the St Maartenskliniek. Data will be stored for 20 years after the end of the study. Patients will be asked for permission to use their data (anonymously) for additional research in the field of PsA, as described in the patient information brochure. An independent monitor will be appointed to monitor the study according to the monitoring plan. Monitoring and quality assurance will be performed according to the advice of the NFU (Dutch Federation of University Medical Centres).

